**Sample Acquisition**

Samples will be obtained by the following methods a schedule of actions will be prepared separately for the participants, describing how and where the stool samples will be submitted, and will be explained to them at the time of obtaining their consent.

1. Stool samples are taken at intervention, 2, 4, and 6 weeks after sake lees consumption to obtain concentrations of uremic substances in stool, short-chain fatty acids, and bacterial flora in stool.
2. Urine samples at intervention and after 6 weeks to obtain urinary pH.
3. Stool and urine samples will be collected at the participant's home using the prescribed kit.
4. At intervention, 2, 4, and 6 weeks after sake lees consumption, blood samples are taken to obtain blood D-amino acid levels.
5. The examinee records the status of sake lees intake daily using an independently prepared record sheet (Appendix 2).
6. Daily recording of defecation frequency and stool characteristics by the examinee using the Bristol Scale^12)^ (Appendix 3).
7. Validated dietary assessment instruments will be administered 2 weeks prior to the intervention and at the end of the intervention (6 weeks later) to assess food intake frequency and nutrient intake.

*4 involves a minor invasion when collecting blood samples. 1, 2, 3, 5, and 6 do not involve physical invasion since they are obtained through stool and urine samples and questionnaires.

**Location of the study**

The examination, blood sampling, and nutritional guidance will be conducted in the Laboratory of Nephrology, Kanazawa University Graduate School of Nephrology. Body composition measurement will be conducted in the Nutritional Counseling Room of Kanazawa University Hospital.

**Data Analysis Method**

The primary endpoint, the concentration of uremic substances in the stool, will be analyzed before and after the intervention using analysis of variance and Dunnett test, two-tailed, at a 5% level of significance.

**Disclosure of Research Results**

At the time of obtaining consent, participants will be asked to confirm their willingness to disclose the results of the research, and if they wish to do so, the results of stool, urine, and blood tests will be disclosed. The method of disclosure will be in writing to the research participant. However, if the request for disclosure is cancelled during the course of the research, no disclosure will be made.

**7. Observation, examination and report items**

Observation and inspection items shall be as follows

**Background of the examinee**

Age (year of birth), gender, height, weight, BMI

**Stool (fecal) examination**

Uremic substances (indole, p-cresol), flora, short-chain fatty acids (acetic acid, lactic acid, propionic acid, butyric acid), pH

**Urinalysis**

　pH (measure of acidity)

**Blood test**

D-Serine, D-Alanine

**Frequency of defecation, stool characteristics**

Bristol Scale, Constipation and Quality of Life Score (PAC-QOL)^13)^  (Exhibit 4)

**Food Intake Frequency and Nutrient Intake Assessment**

Food Frequency of Intake Survey (FFQg)^14)^ (Exhibit 5), Compliance with Liquorice Consumption

**Body composition measurement**

Skeletal muscle mass, trunk muscle mass, limb muscle mass, body fat percentage, body fat mass, body cell mass, extracellular water ratio

**Schedule of Observations and Inspections**

The range of the inspection period shall be no more than 5 days before or after the reference date.

| **Reference Date** | **Before intervention  (-2 weeks)** | **time of intervention** | **2 weeks later** | **4 weeks later** | **After 6 weeks  （at the end of intervention)** |
| --- | --- | --- | --- | --- | --- |
| Visit | **1** | **2** | **3** | **4** | **5** |
| Doctor's Examination | **●** |  |  |  |  |
| Obtaining Consent | **●** |  |  |  |  |
| nutritional guidance | **●** | **●** | **●** | **●** | **●** |
| Food Intake Frequency Survey | **●** |  |  |  | **●** |
| Constipation and Quality of Life Score | **●** | **●** | **●** | **●** | **●** |
| Body composition measurement |  | **●** | **●** | **●** | **●** |
| Stool (fecal) examination |  | **●** | **●** | **●** | **●** |
| Urinalysis |  | **●** |  |  | **●** |
| Blood test |  | **●** | **●** | **●** | **●** |
| Sake Lees intake status |  |  | **every day** | | |
| Frequency of defecation, stool characteristics |  |  | **every day** | | |

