**3. Scientific rationale and basis for the research**

**Study summary and primary endpoints**

The subjects of this study will be patients with chronic constipation and the intervention will be consumption of 25 g/day or 50 g/day of sake-kasu. The control will be pre-intervention, and the primary endpoint will be the percentage change in the concentration of uremic substances (indole and cresol) in the stool after 2, 4, and 6 weeks. The study design will be a single-arm (2-dose) pre/post comparison.

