**Research Procedures**

1. Provide nutritional guidance prior to intervention using our own sake-kasu recipe (Attachment 1).
2. Sake lees 25 g/day or sake lees 50 g/day for 6 weeks
3. Sakekasu (sake lees) from "Kakuma-no-sato", a refined sake sold by Kanazawa University, will be used. The same lot of sakekasu will be provided to the participants free of charge in order to ensure the same conditions for the intervention.
4. Store sake lees in a refrigerator at about 5℃.
5. Participants can choose how to cook sake-kasu from a collection of sake-kasu recipes
6. Outcome items will be assessed at intervention, 2, 4, and 6 weeks
7. The intake of sake lees and defecation should be recorded daily on the record sheet.
8. The timing and frequency of sakekasu intake is not set. For example, 25 g of sakekasu can be consumed in one meal or divided into three meals.
9. During the introduction period (2 weeks) and the intervention period (6 weeks), the consumption of lactic acid bacteria preparations, foods for specified health uses and foods with functional claims that improve the intestinal environment is prohibited. (Fermented foods other than sake lees, such as miso and yogurt (general foods), may be consumed.
10. The same dinner (a frozen home-delivered lunch with controlled nutritional value) on the day before the evaluation
11. Breakfast on the day of evaluation after 2, 4, and 6 weeks will be the same meal containing sakekasu

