**(2) Secondary endpoints**

- Percentage change in the percentage of major bacterial species in stool
- Concentration of short-chain fatty acids (acetic acid, lactic acid, propionic acid, butyric acid) in stool
- Stool pH, stool characteristics, frequency of defecation
- D-amino acid concentration in blood
- Defecation frequency and characteristics, constipation and quality of life score (PAC-QOL)
- Frequency of food intake, amount of nutrients consumed, and percentage of compliance with sake lees

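### As scheduled, the defecation and Bristol stool record starts only once sake lees intake begins, so two secondary endpoints have no pre-intake value, although the text calls for outcome assessment at intervention

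*Protocol*

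**What the plan says.** **Design.** Section 3 of the Protocol states that "The control will be pre-intervention" and that "The study design will be a single-arm (2-dose) pre/post comparison". It also says there is no comparison group and that evaluation takes place four times, the first at the time of intervention. Research Procedures item 6 (section 6(2)) repeats these four time points for the outcome items.

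**Endpoints.** Section 9(2) lists defecation outcomes twice among the secondary endpoints: "Stool pH, stool characteristics, frequency of defecation" and "Defecation frequency and characteristics, constipation and quality of life score (PAC-QOL".

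**Diary.** Research Procedures item 7 says: "The intake of sake lees and defecation should be recorded daily on the record sheet". Sample Acquisition item 6 asks for daily recording with the Bristol Scale. Neither gives a start date. The section 7 schedule is the only place that fixes the timing: "Frequency of defecation, stool characteristics | | | every day". The row directly above has the same layout: "Sake Lees intake status | | | every day".

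**Introduction period.** Research Procedures item 9 restricts certain products "During the introduction period (2 weeks) and the intervention period (6 weeks", so a 2-week period before intake is already part of the plan.

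**The concern.** In a single-arm study each participant's pre-intake value takes the place of a control group. An outcome recorded only during intake can be described over time or compared between the 25 g and 50 g groups, but its change from before intake cannot be estimated.

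Constipation is in the trial title, and the study is meant to inform the amount and duration of intake in a later randomized trial. Stool frequency and form are the direct measures of constipation here. Days that were not recorded before intake cannot be recovered afterwards, so the matter has to be settled before participants start.

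**Working it through.** The protocol gives no figure to reproduce. The check sets the schedule beside the other places that could supply a pre-intake value.

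**1. Pre-intake columns of the schedule (visit 1 at -2 weeks, visit 2 at the time of intervention).**

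- Defecation frequency and stool characteristics: 0 of 2 columns filled. The daily entry covers the 2-, 4- and 6-week columns, 3 of 3.
- Sake lees intake: the same span. Intake cannot be recorded before it starts, so the shared span indicates a record that begins with intake.
- PAC-QOL: 2 of 2 columns filled.
- Stool examination and blood test: filled at visit 2. By section 7 these cover indole, p-cresol, flora, short-chain fatty acids and stool pH, and D-serine and D-alanine.

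**2. Could another item give a baseline for frequency or Bristol type?**

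- The stool examination at visit 2 does not include frequency or form.
- Eligibility (section 4(1)) requires at least two of six yes/no criteria. Only one concerns frequency and only one concerns stool type, so a participant can qualify on the other four. These criteria give no per-participant value in the units of the diary.
- Sample Acquisition item 7 names a time two weeks before the intervention for the dietary questionnaires. Item 6, the defecation record, has no such statement.

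**3. Schedule against text.** Research Procedures item 6 and section 3 require outcome assessment at intervention. Defecation frequency and stool characteristics are outcomes under section 9(2). The schedule assigns them nothing at that time, so the passages disagree. Item 6 also does not say how a daily diary item would be valued at a single visit.

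**4. What an earlier start would add.** With 8 participants (section 5(1)), an introduction period of 2 x 7 = 14 days and an intervention of 6 x 7 = 42 days:

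- baseline diary-days as scheduled: 0
- baseline diary-days with a start at visit 1: 8 x 14 = 112
- diary-days during intake: 8 x 42 = 336

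Section 7 allows each visit up to 5 days either side of its reference date. If only visit 1 moves, the run-in is 14 - 5 = 9 to 14 + 5 = 19 days. If visits 1 and 2 move in opposite directions, it is 14 - 10 = 4 to 14 + 10 = 24 days. These are counts of available data; they say nothing about the size of any bias or effect.

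**The case against.** **The text already calls for a value at intervention.** This stands in part. Item 6 and section 3 do so, and that makes the problem an inconsistency to be reconciled. It does not show that the sponsor meant to have no baseline. But nothing in the protocol schedules the recording that would supply one.

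**The diary may start earlier in practice.** The daily-recording instructions do not forbid it, the record sheets are attachments, and participants are to receive a separate schedule of actions. This also stands in part: one cannot say that no pre-intake diary will exist. Still, that separate schedule is described as covering how and where stool samples are submitted, and the blank cells together with the matching intake row make a start with intake the natural reading.

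**No change score is promised.** Percentage change is specified for the primary endpoint and for bacterial species, and the sentence naming the control belongs to the account of the primary endpoint. That is correct. But the whole study is described as a before/after comparison with no comparison group, so values during intake alone would not answer its question for these outcomes.

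**A statistical analysis plan could deal with it.** It could define a baseline from collected data, but it cannot supply days that were never recorded.

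**Stronger readings.** A reader might infer that constipation as a whole has no baseline, or that the main result is compromised. The documents do not support this: PAC-QOL is scheduled at both pre-intake visits, and the primary endpoint has its value at visit 2. A reader might also infer a biased result, through recalled frequency or the first weeks of intake being used as baseline, or through regression to the mean. The protocol proposes neither substitute. Its requirement of symptoms for at least 6 months, with the criteria met for the last 3, lessens selection on a brief flare without removing it. No size of bias can be derived from the documents.

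**Conclusion.** The point holds as a moderate defect confined to two secondary endpoints. The schedule starts the defecation and Bristol record only with intake, while the text calls for outcome assessment at intervention and the only control is the pre-intervention state. Followed as written, the schedule yields 0 pre-intake diary-days, and no within-subject change in defecation frequency or stool characteristics can be computed.

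This rests on two assumptions: that the daily entry in the schedule begins at the 2-week column, as the blank cells and the identical intake row indicate, and that the attachments and the participants' separate schedule do not set an earlier start. If they do, the data problem disappears and only the protocol wording needs correction.

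The matter does not threaten the study's main purpose. This is an eight-person pilot, sized on feasibility, that centres on stool metabolites and flora.

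**What to change.** Start the existing defecation and Bristol record sheet at visit 1, so that the introduction period supplies the baseline. Three places need amending so that they agree:

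- **Schedule of Observations and Inspections:** extend the daily entry for defecation frequency and stool characteristics back to visit 1, and leave the sake lees intake row as it is.
- **Research Procedures items 6 and 7:** separate the defecation record from the intake record, state that the former starts at visit 1, and say that for diary items the assessment at intervention is drawn from the introduction period.
- **Sample Acquisition item 6:** give the same start.

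Because the visit window can shorten the run-in, the amendment should describe the baseline as the days actually recorded between visit 1 and the start of intake, nominally 14. How those days are summarised can be left to the statistical analysis plan.

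The cost is about 14 more diary days per participant, nominally 112 across the eight, and handing out the sheet two weeks earlier at a visit that already takes place. No visit, sample or instrument is added. The change needs ethics committee approval under section 16. It helps only participants who have not yet begun intake.

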**8. evaluation and reporting of adverse events**

**(1) Definition of adverse events and reporting methods**

☒ N/A

☐ Yes

This study involves minor invasive procedures as blood samples will be drawn before and after the intervention. The condition of the study subjects will be thoroughly observed during the blood draw, and the blood draw will be stopped if there is any discomfort.

Sake lees is a food that is consumed on a daily basis, and adverse events are not expected to occur due to its consumption. However, in the event of an undesirable change in physical condition, the researcher should consult with the physician in charge of the research through the contact person and take appropriate measures. If the physician determines that it is difficult to continue the research, the consumption of sake lees will be discontinued and the matter will be reported to the department head.

**(2) The burdens and anticipated risks and benefits to the research subjects, a comprehensive assessment of these burdens and risks, and measures to minimize such burdens and risks**

**(1) Projected profit**

There will be no direct benefit to individual research subjects from participating in this study. Research results may contribute to the advancement of medical care. As a reward, a QUO card (up to 20,000 yen) will be given in accordance with the University's regulations at the end of the research.

Sake lees will be provided free of charge to the research subjects because it is necessary to use the same product and the same lot of sake lees in order to match the intervention conditions.

**(2) Anticipated risks and disadvantages**

This study involves minor invasive procedures as blood samples will be drawn before and after the intervention. The condition of the study subjects will be thoroughly observed during the blood draw, and the blood draw will be stopped if there is any discomfort.

Since sake lees contain trace amounts of alcohol, driving a car after consumption of sake lees with insufficient alcohol volatilization may constitute driving under the influence of alcohol. The use of sakekasu with sufficiently volatilized alcohol by adhering to the cooking method according to the protocol should be emphasized in nutritional guidance during the intervention.

**9. Evaluation items**

**(1) Primary endpoint**

Percent change in concentrations of uremic substances (indoles and cresols) in stool

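### The protocol defines the primary endpoint as percent change but names and tests concentration; each reading has its own fault, and one log-scale within-participant endpoint would replace both

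*Protocol*

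**What the plan says.** Three places in the protocol fix the primary variable.

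- Section 9(1), Primary endpoint: "Percent change in concentrations of uremic substances (indoles and cresols) in stool".
- Section 3, Study summary and primary endpoints: "the percentage change in the concentration of uremic substances (indole and cresol) in the stool after 2, 4, and 6 weeks". The same paragraph sets the comparator: "The control will be pre-intervention".
- Section 6(2), Data Analysis Method: "The primary endpoint, the concentration of uremic substances in the stool, will be analyzed before and after the intervention". The named method is an ANOVA with Dunnett comparisons, two-sided at 5%.

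Measurements are taken at four times (section 6(2), Research Procedures: "Outcome items will be assessed at intervention, 2, 4, and 6 weeks"), so a Dunnett test against baseline has three contrasts. The target is eight participants, set on feasibility (section 10). The protocol does not say how a percent change is calculated or summarised, and it mentions no log or ratio scale. A related construction appears among the secondary endpoints in section 9(2): "Percentage change in the percentage of major bacterial species in stool".

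**The concern.** The variable defined as the primary endpoint has no stated analysis, and the variable that is analysed is not the one defined. The protocol itself fixes both the endpoint and the test, so this is not detail left to a statistical analysis plan. Two analysts, one working from section 9(1) and the other from the Data Analysis Method, could report different primary results from the same eight people.

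Taking either statement at face value does not settle the matter, because each variable has a weakness with the named test. The study looks for a fall in stool indole and cresol, and its results are meant to set the amount and duration of intake in a later trial in chronic kidney disease. A scale that masks or blurs a fall therefore matters even in a pilot.

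**Working it through.** **Inputs from the protocol:** n = 8, four visits, three contrasts against baseline, two-sided 5%. There is no effect size, SD or power figure to reproduce.

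**Assumptions:** lognormal concentrations; independent within-person error at each visit with log-SD s; between-person log-SD 0.7; all eight analysed together; the same true reduction r at weeks 2, 4 and 6. The within-person CV satisfies CV² = exp(s²) − 1. The protocol gives no CV, so a range is shown.

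**1. Percent change entered in the Dunnett test.** At baseline, 100 × (Y₀/Y₀ − 1) = 0 for every participant. The control has variance exactly 0, and the equal-variance assumption fails by construction.

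**2. Averaging individual arithmetic percent changes.** Person effects cancel in Y/Y₀. The log of the ratio has variance 2s², so with no effect E[Y/Y₀] − 1 = exp(s²) − 1 = CV². With a true reduction r, the expected percent change is (1 − r)(1 + CV²) − 1.

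| CV | No effect | True 20% fall | True 30% fall |
|---|---|---|---|
| 20% | +4% | 0.8 × 1.04 − 1 = −16.8% | 0.7 × 1.04 − 1 = −27.2% |
| 30% | +9% | 0.8 × 1.09 − 1 = −12.8% | 0.7 × 1.09 − 1 = −23.7% |
| 50% | +25% | 0.8 × 1.25 − 1 = 0% | 0.7 × 1.25 − 1 = −12.5% |
| 80% | +64% | 0.8 × 1.64 − 1 = +31.2% | 0.7 × 1.64 − 1 = +14.8% |

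**3. Power to declare a decrease, with one error term for all three scales.** For visit k, t = (mean at k − mean at baseline) / √(2 × MSE/8). The MSE comes from the participant-by-visit residual, with 3 × 7 = 21 degrees of freedom, and the simulated Dunnett critical value is about 2.53. Simulated power:

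| CV, true reduction | Percent change | Raw concentration | Log concentration |
|---|---|---|---|
| 50%, 50% | 67% | 70% | 86% |
| 50%, 30% | 17% | 24% | 34% |
| 20%, 30% | 93 to 94% | 86% | 96% |

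**4. False positives with no effect (same error term, CV 50%).** Percent change declares an increase in 5.8% of trials and a decrease in 0.7%. Across within-person log-SDs of 0.2 to 0.7, its family-wise error is 0.056 to 0.072. Raw concentration gives 0.033 to 0.037 and log concentration 0.051 to 0.052; on the log scale, rejections split about evenly between the two directions.

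**The case against.** The strongest reply is that the mismatch has an ordinary reading: concentrations are tested against baseline and the effect is reported as a percent change. That reading is sensible, and the fix below makes it explicit. As written, though, the protocol names two different variables as the primary endpoint, so the contradiction stands.

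Four stronger readings are tempting, and the document does not support them.

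- *The plan uses a control with no variance.* No section puts percent change into the Dunnett test. The Data Analysis Method tests concentration, and baseline concentration varies. The zero-variance control and the weakness of raw concentration belong to different readings and do not occur together.
- *The endpoint as stated hides reductions.* The bias applies to a mean of individual arithmetic percentages, and the protocol does not say that this is the summary. At CV 50% with no effect, the median of eight percent changes averages about +5% and the percent change in the population mean is about 0. With a true 20% fall, the corresponding figures are about −16% and −20%.
- *The choice of scale costs as much as 57% against 86% power.* Those figures arise at CV 50% and a true 50% reduction if a one-way Dunnett on percent change is set against a within-participant log analysis. Part of that gap comes from ignoring the pairing. With a one-way error term throughout, percent change (57%) does better than log (26%) or raw concentration (about 30%). Pairing is a separate matter from scale, which is why the table uses one error term.
- *Percent change would produce false claims of benefit.* Its false positives run mostly towards an increase, and its family-wise error stays at or below about 0.07 in these scenarios.

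The study is also a feasibility-sized pilot, which limits the consequences.

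**Conclusion.** The contradiction between sections 3 and 9(1) on one side and the Data Analysis Method on the other is certain from the text and should be resolved before analysis. How much it matters numerically is conditional. At an assumed within-person CV of 50%, testing percent change or raw concentration instead of log concentration costs 16 to 19 percentage points of power for a true 50% reduction (86 − 70 and 86 − 67), and 10 to 17 points for a true 30% reduction (34 − 24 and 34 − 17). At CV 20%, percent change and log are nearly equal, and the upward bias is about 4%. These figures rest on lognormal, independent within-person error, a between-person log-SD of 0.7, all eight participants pooled, and a within-participant error term. The protocol supplies none of the variances. The main risk is a masked reduction and an ambiguous primary result, not a false finding of benefit.

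The bacterial-species endpoint is a lesser point: a percent change from a baseline of zero is undefined. This matters only if a species counted as major is undetected in someone at baseline.

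**What to change.** In section 3, the Data Analysis Method in section 6(2), and section 9(1), name the same primary variable: log stool concentration at weeks 2, 4 and 6 against the participant's own baseline. Analyse it within participant (participant as a block) with Dunnett-adjusted contrasts, two-sided at 5%. Report 100 × (geometric mean ratio − 1) with its 95% confidence interval and call that the percent change. The reporting language of sections 3 and 9(1) is kept, and the test then addresses the same quantity.

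For the bacterial-species secondary endpoint, use the change in percentage points, or a log-ratio measure with a stated rule for zeros, where a species may be undetected at baseline.

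The cost is a wording change in three places and one secondary item, with no new samples or visits. The small downside is that values below the detection limit need a stated substitution before logs are taken.
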